### Trial Arm Description

Participants are randomized equally to the 2 treatment arms, which include an enhanced usual care control arm as well as the MI-BP intervention arm.

#### Comparison Group: Enhanced Usual Care

The usual-care participants are given a prescription for antihypertensive medications, printed educational materials on HTN, and a home BP monitor for daily use, but they receive no further intervention (see Table 1); however, the participants take part in all study-specific follow-up visits. Although not all patients with HTN consistently utilize home BP monitoring, it is widely accepted as a guideline-based standard of care, making it appropriate to include in the usual care arm.

**Figure 2 figure2:**
[figure not shown]
Trial procedure flow diagram.

**Table 1 table1:** Trial arms.

Components: intervention component	Trial arm	
	Usual care	Usual care + MI-BP
Prescription for hypertension medication	Yes	Yes
Referral to primary care if needed	Yes	Yes
Home blood pressure monitoring	Yes, but no digital tracking tools	Yes, with digital tracking tools via MI-BP app
Physical activity monitoring	No	Yes, with Fitbit or MI-BP app
Sodium intake self-monitoring	No	Yes, with MI-BP app
Medication reminders	No	Yes, with MI-BP app
Patient education materials	Yes, via pamphlet	Yes, with pamphlet or MI-BP app
Goal setting and motivational messages	No	Yes, with MI-BP app
Medication titration and data collection visits at weeks 2, 8, 13, 26, 39, and 52	Yes	Yes

#### Intervention Group: MI-BP, Technology-Enhanced Self-Monitoring

MI-BP participants receive an antihypertensive medication prescription and are asked to use the MI-BP intervention described above for 12 months.

### Measures

Throughout this study, we are collecting a variety of different measures to help determine the feasibility and efficacy of MI-BP including BP, physical activity, sodium intake, and medication adherence. Given the number of measures we are assessing in this trial, our primary data collection visits at baseline and weeks 13, 26, 39, and 52 are lengthy and take about 90 min to complete. To reduce the effect of potential response fatigue because of participant burden, we have divided our surveys into sections focused on measures pertaining to BP, physical activity, and sodium intake, and block orders are randomized among participants. The remaining data collection visits are 30 min or less in duration. While we are collecting a range of measures to ascertain intervention efficacy, our main outcome is differential BP change over time. Other measures will be included as covariates in the modeling of our main outcome and analyzed independently as exploratory end points. In this way, we will be able to capture information on the mediators of our main outcome along with independent effects on specific aspects of self-management.

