**Objective:**

The MI-BP app aims to reduce health disparities related to HTN in the community by employing a user-centered intervention focused on self-BP monitoring, physical activity, reduced sodium intake, and medication adherence. We seek to test the efficacy of MI-BP, an mHealth app for HTN self-management, on BP control (primary aim), physical activity, sodium intake, and medication adherence (secondary aim) in African Americans with HTN. This study also seeks to evaluate the cost-effectiveness of MI-BP when compared with usual care methods.

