**Methods:**

This is a 1-year randomized controlled trial that will recruit individuals who have uncontrolled HTN from 2 EDs in the city of Detroit, with a planned sample size of 396 randomized participants. To be eligible for inclusion, potential participants must be African American, 25 to 70 years old, previously diagnosed with HTN, have a smartphone compatible with MI-BP, and have uncontrolled BP at triage and on repeat measurement at least 1-hour post triage vitals. Once a participant is deemed eligible, all study procedures and subsequent follow-up visits (8 in total) are conducted at the Wayne State University Clinical Research Service Center. We seek to determine the effect of MI-BP on BP for 1 year (using BP control and mean systolic BP as coprimary outcomes and physical activity, sodium intake, and medication adherence as secondary outcomes) compared with usual care controls.

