Randomization is stratified by sex in blocks of equal size, allowing us to investigate sex as an effect-modifying biological variable. To control response fatigue, we created 6 different permutations of the baseline survey, each with a different order of instruments, which are also balanced within blocks. The research assistants responsible for arm allocation are blinded to block size to prevent contamination.

After randomization, all study materials, including any equipment and/or materials, are distributed to the participants according to the treatment arm. Medication titration occurs again at week 8, and at subsequent follow-up visits at weeks 13, 26, 39, and 52 to ensure optimal treatment. Data collection follow-up visits take place at weeks 13, 26, 39, and 52, where a consistent set of study measures is collected—BP, health status, weight, adherence to BP measurements, physical activity, sodium intake, and medication adherence self-monitoring. Technology acceptance measures, including perceived ease of use and perceived usefulness, are also collected.

For medication titration and follow-up visits, patients are instructed to bring their HTN medications with them so pill counts can be conducted. Pill counts are used to avoid prescribing potentially harmful up-titration in antihypertensive therapy for patients with elevated BP at follow-up visits that may be because of medication noncompliance. For patients who self-report not filling prescriptions between visits, or when the expected number of pills found in the participant’s medication bottles (based on dosage and dispense date) suggests a less than 80% medication adherence, we continue with the same regimen without adjustment. We also monitor for any potentially harmful renal or metabolic issues at weeks 0, 26, and 52 and adjust medications accordingly. In addition to the medications, participants are instructed to bring study-dispensed devices so data can be downloaded, and adherence to self-monitoring behaviors can be ascertained.

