### Statistical Analysis Plan

#### Analysis of Blood Pressure Control

To determine the effect of MI-BP on BP at 1 year (aim 1) and to determine whether BP control is better in intervention-group participants compared with controls (hypotheses 1a), we will conduct a comparative analysis using a logistic regression with BP control as the outcome and study arm as the primary factor, controlling for demographic characteristics such as age, gender, medical history, baseline levels of functional status, health literacy, HTN knowledge, self-efficacy, and baseline BP at randomization. To determine whether mean SBP is better in the intervention group, compared with controls (hypothesis 1b), differential reduction in the coprimary outcome of SBP will be assessed in a linear mixed-effects regression framework, with time (baseline and end-of-trial), group, and time-by-group interaction as the primary independent variables. The subject-level characteristics used in the analysis of the primary outcome will be controlled in the regression model.

To determine the effect of MI-BP on secondary outcomes (aim 2), we will also use linear mixed-effects regression models with the secondary outcomes of interest as the dependent variables and week (as a continuous variable), study group, and week-by-group interaction as the primary independent variables. All appropriate model diagnostics will be carried out.

During data analysis, we will statistically address missing data resulting from incomplete data collection or participant attrition using the multiple imputation technique. Missing values will be imputed by repeatedly and iteratively fitting a sequence of regression models; it is a technique that is flexible in allowing different types of variables (categorical and continuous) to be imputed together without requiring any multivariate joint distributional assumption. Missing values are sequentially updated using bootstrap or Markov Chain Monte Carlo based on multiple regression models with other variables as covariates. This procedure will be conducted for 10 repetitions or cycles, a number considered adequate for most applications, thereby constructing an *imputed* dataset. Results from the 10 regressions will be combined with the imputed data using Rubin’s formula [39].

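### The Measures section and the analysis section conflict on the covariates of the primary BP models; the Measures wording, if applied to those models, would replace the total effect with a residual direct effect

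*Protocol article*

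**What the plan says.** The Measures section introduces the data collected "to help determine the feasibility and efficacy of MI-BP including BP, physical activity, sodium intake, and medication adherence". It states that "our main outcome is differential BP change over time", then that "Other measures will be included as covariates in the modeling of our main outcome and analyzed independently as exploratory end points". The reason follows: "In this way, we will be able to capture information on the mediators of our main outcome along with independent effects on specific aspects of" how participants manage their condition.

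The section Analysis of Blood Pressure Control specifies the coprimary models. The logistic model for BP control has study arm as the main factor and adjusts for age, gender, medical history and "baseline levels of functional status, health literacy, HTN knowledge, self-efficacy, and baseline BP at randomization". The SBP mixed model (time, group, time by group) carries the same subject-level characteristics. Neither model names a follow-up value of activity, sodium intake or medication adherence.

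The status of those three measures also differs between sections. The Abstract describes the trial as "using BP control and mean systolic BP as coprimary outcomes and physical activity, sodium intake, and medication adherence as secondary outcomes". Study Objective and the analysis section agree that they are secondary, whereas the Measures sentence calls the other measures exploratory.

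**The concern.** Activity, sodium intake and adherence are what the app sets out to change. The Abstract describes a "user-centered intervention focused on self-BP monitoring, physical activity, reduced sodium intake, and medication adherence". Randomisation is at week 2, and Procedures says "Data collection follow-up visits take place at weeks 13, 26, 39, and 52, where a consistent set of study measures is collected". Follow-up values of these measures are therefore consequences of randomisation, and the Measures section itself calls them mediators.

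Aim 1 asks for the effect of MI-BP on BP compared with usual care, which is a total effect. Holding follow-up behaviour fixed in that model removes whatever part of the effect runs through the behaviour. What remains is a direct effect that randomisation no longer protects, because any common cause of behaviour and BP then confounds it. Entering mediators as covariates is also not, by itself, a mediation analysis.

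Two covariate sets for one primary analysis also leave room to choose after the data are seen, and the two choices answer different questions.

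**Working it through.** **1. The sections side by side**

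| Point | Measures | Analysis of Blood Pressure Control |
|---|---|---|
| Outcome modelled | Differential BP change over time | BP control at 1 year; differential SBP reduction |
| Covariates | The other measures, to capture mediators | Demographics, medical history, baseline functional status, literacy, knowledge, self-efficacy, baseline BP |
| Status of activity, sodium, adherence | Exploratory, if they are among the other measures | Secondary |

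A baseline value cannot carry information about mediation, so the stated purpose in Measures needs follow-up values. The analysis section provides for none.

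**2. The plan's own figures (Sample Size)**

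Inputs: control rates 30% and 47.5% (30 + 17.5 points), two-sided 5%, 90% power; SBP falls of 10 and 17 mmHg, SD 10, correlation 0.5, 161 per arm.

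- BP control: n = [1.96·√(2 × 0.3875 × 0.6125) + 1.2816·√(0.30 × 0.70 + 0.475 × 0.525)]² / 0.175² = 160.8, so 161 per arm. Power at 161 is 0.900. The plan's figure is reproduced.
- SBP: SD of change = 10·√(2 × (1 − 0.5)) = 10; SE = 10·√(2/161) = 1.115; 7/1.115 − 1.96 = 4.32, so power is above 0.999. This agrees with the stated figure of more than 95%.

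No sample-size figure is disputed here.

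**3. Size of the change if mediators were entered**

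The mediated share m is not in the documents and is assumed over a range. For SBP the residual effect is 7 × (1 − m). For BP control the planned odds ratio is (0.475/0.525)/(0.30/0.70) = 2.11, and the residual is 2.11^(1 − m), applied to the 30% control rate. Power uses the formulas of step 2.

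| m | SBP effect (mmHg) | Power | BP control OR | Rate, MI-BP arm | Power |
|---|---|---|---|---|---|
| 0 | 7 | >0.999 | 2.11 | 47.5% | 0.90 |
| 25% | 5.25 | 0.997 | 1.75 | 42.9% | 0.67 |
| 50% | 3.5 | 0.88 | 1.45 | 38.4% | 0.35 |
| 75% | 1.75 | 0.35 | 1.21 | 34.1% | 0.12 |

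The log-odds scaling is a rough device.

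**4. Simulation check for SBP**

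Set-up: 161 per arm, 1,500 runs, a mediator shifted by 1 SD between arms, no mediator-outcome confounding. Adjusting for baseline SBP only, the mean estimate was −7.00, −7.01 and −6.97 mmHg at m = 25%, 50% and 75%. Adding the mediator gave −5.25, −3.52 and −1.75 mmHg. The shift in the quantity estimated is as computed.

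Simulated power with the mediator was 0.999, 0.946 and 0.524, higher than in the table at 50% and 75%. The simulation adjusts for baseline, so residual variance is 100 × (1 − 0.5²) = 75 and not 100. The mediator then explains (7m)² of that variance, while its correlation with arm inflates the variance of the arm coefficient by 1.25 (mediator variance 1.25 overall, 1 within arm). At 50% this gives (75 − 12.25) × 1.25 = 78.4, so nearly all of the gain over 0.88 comes from baseline adjustment. At 75% it gives (75 − 27.56) × 1.25 = 59.3, so both contribute. The SBP powers in the table are therefore approximate; the change in the quantity estimated is the firmer result.

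**The case against.** The strongest reply is that the analysis section governs. It sits under the Statistical Analysis Plan heading, names both coprimary models and lists their covariates, and an analyst who follows it estimates the total effect. Measures is a general introduction to data collection. Its sentence does not say that follow-up values are meant. Functional status, health literacy, hypertension knowledge and self-efficacy are all described under Measures, and their baseline values are what the analysis section enters. Activity, sodium intake and adherence are measured at baseline too. Modelling the main outcome can also mean a separate model: the end of the cost-effectiveness section places adherence to self-monitoring, a post-randomisation variable, in a BP model presented as additional to the stated aims.

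Much of this stands. A reader might infer that the primary analysis is fixed as mediator-adjusted and its estimate therefore biased. The documents do not support that, because the only detailed specification uses baseline and subject-level covariates. A reader might also infer a certain bias towards no effect. Attenuation is likely if the app works through these behaviours, but mediator-outcome confounding can act in either direction. The label mismatch is minor, since the other measures also include items, such as patient activation, for which exploratory may be right.

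The reply does not remove the conflict. Measures describes its outcome in nearly the same terms as the SBP coprimary analysis, does not mark its covariate model as separate, and calls only the independent analyses exploratory. The covariate list in the analysis section is introduced by way of example, so it does not expressly exclude others. The additional analysis concerns logging of self-monitoring, not the measures at issue, and no mediation analysis is named anywhere. Nor is this a detail left to a fuller document: the article makes two statements that do not agree.

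**Conclusion.** The point holds as a conflict between two sections on the covariates of the primary analysis, and it should be fixed. It does not show that the coprimary models are mis-specified.

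The harm is conditional on the Measures sentence being applied to those models with follow-up behaviours. Aim 1 would then be answered with a residual direct effect. Mediated shares of 25% to 75% would shrink the planned 7 mmHg to between 5.25 and 1.75 mmHg. BP control has less room: its planned power of 0.90 would fall to between 0.67 and 0.12 on the log-odds scaling. These figures rest on assumed mediated shares, on the plan's SD and correlation, and on no mediator-outcome confounding. They illustrate scale and do not predict the trial's result.

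**What to change.** - In Analysis of Blood Pressure Control, state that both coprimary models adjust only for variables measured before randomisation, and close the list. In the SBP mixed model, baseline SBP is already an outcome time point and need not also be a covariate.
- In Measures, keep the sentence but limit its scope. For example: *Baseline values of selected other measures enter the coprimary models as listed in the analysis section. Follow-up values do not; they are examined in a separate, explicitly exploratory mediation analysis.* Retain the statement that the measures are also analysed in their own right.
- Call physical activity, sodium intake and medication adherence secondary outcomes throughout, and keep exploratory for the remaining measures.

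The cost is wording only. No new data, visits or participants are needed, and the sample size is unaffected.

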#### Blood Pressure

We are collecting 2 types of BP data in this trial: in-clinic and home BPs. In-clinic BPs are assessed for every patient, regardless of trial arm, at every study visit by a trained study staff member using a BpTRU BP monitoring device. Home BP data are also collected from the intervention-group participants as a part of their use of the MI-BP app.

#### Physical Activity

A total of 2 different types of physical activity data are collected in this trial. All the participants, regardless of treatment arm, complete the International Physical Activity Questionnaire at baseline and weeks 13, 26, 39, and 52 [27]. In addition, the participants randomized to the MI-BP intervention group are instructed to wear their Fitbit Zip pedometer daily and asked to sync their Fitbit Zip using the Fitbit app at least once per week, which allows the MI-BP app to obtain their physical activity data.

#### Sodium Intake

Sodium intake is measured by 3 different ways. All the participants, regardless of treatment arm, are asked to complete the Block Sodium Screener at weeks 0, 13, 26, 39, and 52 [28], as well as a 24-hour urine sodium test at baseline and weeks 26 and 52. The latter provides an objective measure of the actual total daily sodium intake load. To complete the 24-hour sodium assessment, participants are provided collection materials during study visits and instructed to start their urine collection the following morning. The participants are instructed to start the 24-hour collection time immediately after the first-morning urination, which is discarded and not included in the collection. Participants collect all voided urine for the remainder of the day and night. The next morning, at the same time as day 1, participants collect the first-morning urine and add this to the total, so that a full 24-hour urine has been collected. Participants are instructed to store their specimen in the refrigerator during and after the collection process. Finally, the intervention-group participants are asked to periodically self-monitor their intake of high-sodium foods using a checklist approach, as previously described.

#### Medication Adherence

Medication adherence is measured by 3 different methods to gain a highly comprehensive approach to assess medication adherence, offsetting the weakness of each individual measure in the process.

##### Pill Counts

Participants are asked to bring all HTN medications to follow-up visits at weeks 2, 8, 13, 26, 39, and 52 so that pill counts can be conducted. Participants will be considered adherent if the number of pills remaining in the bottle is within 20% of the expected amount.

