### Study Objective

The purpose of this study is to establish the efficacy of MI-BP, a multiple behavior change intervention delivered via mHealth that supports achieving and maintaining BP control in African Americans who have uncontrolled HTN and are recruited from 2 urban EDs. This study also seeks to evaluate the cost-effectiveness of MI-BP compared with enhanced usual care methods.

Our primary study aim is to determine the effect of MI-BP on BP for 1 year (using BP control and mean systolic blood pressure [SBP] as coprimary outcomes) compared with usual care controls, in a 1-year randomized controlled trial (RCT) (NCT02955537). We hypothesize that at 1 year, BP control rates will be significantly greater in the MI-BP arm than in usual care. We also hypothesize that at 1 year, mean SBP will be significantly lower in the MI-BP arm than in usual care. Our second aim is to determine the effect of MI-BP on secondary outcomes (physical activity, sodium intake, and medication adherence) compared with usual care controls, in a 1-year RCT. We hypothesize that at 1 year, measures of physical activity, sodium intake, and medication adherence will be significantly better in the MI-BP arm than in usual care. Our third aim is to evaluate the cost-effectiveness of MI-BP compared with usual care methods. We hypothesize that the MI-BP approach will provide good value for money, both within-trial and long term. Here we describe the MI-BP approach that was developed for this study.

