### Procedures

Once enrolled and consented in the ED (weeks −1 to −2), participants are scheduled for a return visit in 1 to 2 weeks for their baseline appointment (week 0) at the WSU CRSC. As noted above, only those individuals with persistent uncontrolled HTN at this visit are eligible to remain in the study. Baseline data collection also occurs at week 0, and participants are given a prescription for antihypertensive therapy, and referrals to primary care are made by study physicians. For the participants already taking antihypertensive medications and who have an existing relationship with a primary care provider (PCP), we contact their PCP to inform them of our algorithm-based approach to antihypertensive therapy and work to coordinate any medication adjustments. In week 2, participants undergo medication titration, the process of adjusting antihypertensive medication dosages to ensure appropriate and optimal treatment, and are then randomized into 1 of the 2 study arms. Please see Multimedia Appendix 2 for the medication algorithm used in this trial for titration. From our previous unpublished work, we have determined that attrition is greatest between ED recruitment and the first follow-up visit. Thus, by delaying randomization until after this run-in period, we anticipate fewer participants will be lost to follow-up. Moreover, to reduce attrition, at baseline, we collect contact information for up to 3 alternate contacts, who we may call if we are unable to locate the participant to schedule data collection visits. Our staff also heavily rely on telephone calls and text messaging to participant smartphones to communicate as needed to coordinate scheduling, which tend to be the preferred modes of communication among participants. If needed and requested by participants, we also provide transportation to data collection visits. The MI-BP study staff take a participant-centered approach to trial management and are available daily to meet participant needs. Participants are encouraged to call the staff for any questions pertaining to their medications, their BP, technical issues with the intervention, or other issues that arise (see Figure 2 for a flow diagram of trial procedures). Peer-review report from the Center for Scientific Review has been provided in Multimedia Appendix 3.

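### The pill-count rule puts its 20% tolerance on pills remaining, so the intake it accepts as adherent shifts with fill size and days since dispensing

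*Protocol article*

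**What the plan says.** Study Objective lists medication adherence among the "secondary outcomes (physical activity, sodium intake, and medication adherence") with a hypothesis of its own. The Medication Adherence section adds: "Medication adherence is measured by 3 different methods to gain a highly comprehensive approach to assess medication adherence". The three are pill counts, a self-report scale and a blood assay.

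Pill Counts schedules counts at weeks 2, 8, 13, 26, 39 and 52 and defines the result: "Participants will be considered adherent if the number of pills remaining in the bottle is within 20% of the expected amount".

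Procedures uses the same counts for a different purpose. There the expected number is "based on dosage and dispense date", and where the count "suggests a less than 80% medication adherence, we continue with the same regimen without adjustment". That criterion is expressed as adherence, whereas the one in Pill Counts is expressed as pills left.

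The article gives no quantity dispensed and no refill rule.

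**The concern.** A tolerance of 20% is normally meant to separate people who took at least about 80% of their doses from those who did not. A band around the remaining count does something else. Its width is a fifth of whatever should still be in the bottle, so it is wide just after a fill and shrinks to nothing as the bottle empties. Two participants with the same intake can then be classed differently only because their bottles were of different size or were counted at different times after dispensing.

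At stake is how well one stated measure of a secondary outcome classifies participants, and whether two sections using the same counts agree on who is adherent.

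**Working it through.** The article gives no figure derived from this rule, so there is nothing to reproduce first. The sample size does not depend on it.

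**Inputs from the article**
- Rule: remaining count within 20% of the expected count (Pill Counts).
- Counts at weeks 2, 8, 13, 26, 39 and 52 (Pill Counts). The prescription is given at week 0 (Procedures: "Baseline data collection also occurs at week 0, and participants are given a prescription for antihypertensive therapy"), so the gaps are 14, 42, 35, 91, 91 and 91 days.
- Comparison criterion: adherence below 80% (Procedures).

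**Assumptions, since the article does not say:** one pill a day, a single fill, and fill sizes of 30, 60 or 90 pills.

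**Formulas.** Let S be pills dispensed, d doses due, E = S − d the expected remainder, and m doses missed. The bottle then holds E + m.
- Accepted if m ≤ 0.2 × (S − d).
- Intake = (d − m)/d, so the lowest accepted intake is 1 − 0.2(S − d)/d = 1.2 − 0.2 × S/d, floored at zero.
- Setting this to 0.8 gives 0.4 = 0.2 × S/d, so d = S/2.
- A participant who took nothing (m = d) passes when d ≤ 0.2(S − d), that is d ≤ S/6.
- One missed dose fails when 1 > 0.2 × E, that is E < 5.
- With E = 0 there is no percentage to compute.

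**Results in whole pills**

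| Fill S | Day d | Expected left E | 0.2 × E | Most misses accepted | Lowest accepted intake |
|---|---|---|---|---|---|
| 30 | 14 | 16 | 3.2 | 3 | 11/14 = 78.6% |
| 60 | 14 | 46 | 9.2 | 9 | 5/14 = 35.7% |
| 90 | 14 | 76 | 15.2 | 14 (all) | 0/14 = 0% |
| 90 | 28 | 62 | 12.4 | 12 | 16/28 = 57.1% |
| 90 | 42 | 48 | 9.6 | 9 | 33/42 = 78.6% |
| 90 | 56 | 34 | 6.8 | 6 | 50/56 = 89.3% |
| 90 | 84 | 6 | 1.2 | 1 | 83/84 = 98.8% |
| 30 | 28 | 2 | 0.4 | 0 | 28/28 = 100% |

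Late in a fill the rule is very strict. With 30 pills at day 28, one missed dose leaves 3 against 2 expected, a 50% deviation, so 27/28 = 96.4% intake is non-adherent. With 90 pills at day 84, two missed doses leave 8 against 6, a 33% deviation, so 82/84 = 97.6% is non-adherent. A 90-pill fill counted at the end of a 91-day gap should be empty, and the rule then gives no answer.

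**Against the Procedures criterion.** The 90-pill, day-14 non-taker has 0% intake, which is below 80% under Procedures but adherent under Pill Counts. The 30-pill, day-28 participant at 96.4% is above 80% but non-adherent under Pill Counts. The sections can disagree in both directions.

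**With the tolerance on doses.** A non-taker scores 0% for every fill size and day. One missed dose of 28 scores 96.4% and is adherent, as is one missed dose for any d of 5 or more (4/5 = 80%).

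**The case against.** The strongest reply is that the wording is loose shorthand for 80% of doses taken. Procedures speaks of adherence below 80% from the same counts, and a condensed article may leave the working formula to a fuller document. That is a plausible account of the intent. It does not rescue the sentence, which states a definition and names the pills remaining. If 80% of doses was meant, the sentence should say so.

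A reader might infer that people who take nothing will commonly be classed as adherent. The article does not support that. It requires a count within the first sixth of a fill. With a 30-pill fill at day 14, a non-taker has 30 left against 16 expected, 87.5% off, and fails. For a fill begun at the previous visit, the shortest later gap of 35 days would need at least 6 × 35 = 210 pills. The 90-pill case at week 2 precedes randomization according to Procedures, so it cannot reflect an effect of the app.

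A reader might also infer bias between arms through reminders that alter refill timing. Medication Reminders describes daily reminders to take medication, and no section describes refill prompts. Differential error is possible, but nothing in the article shows it or gives its direction.

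Nor can one say that a yes/no label is being forced into a linear model. The Statistical Analysis Plan section names linear mixed models for secondary outcomes without saying which adherence variable enters them.

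Finally, a titration criterion and an outcome label may legitimately differ. That stands as to thresholds. It does not explain why one is expressed in doses and the other in pills left.

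**Conclusion.** The definition is wrong as written. Its implied intake threshold moves with fill size and time since dispensing and matches 80% only when half the fill is due. Under the assumed once-daily fills, it runs from 0% to 78.6% at day 14 and reaches 100% when fewer than 5 pills should remain. The algebra needs only once-daily dosing and a single fill; the worked values also rest on assumed fill sizes. How often participants would be misclassified cannot be calculated without the actual fills.

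The consequence is contained. Pill count is one of three adherence measures, adherence is secondary, and the coprimary outcomes and sample size are untouched. The other two measures do not fully replace it, since the assay is not drawn at weeks 2 or 8. If the quantities behind each count are kept, the result can be recalculated at analysis. Severity: minor to moderate.

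**What to change.** Replace the defining sentence in Pill Counts with one on doses, for example: *pill-count adherence is the number of doses taken (dispensed minus remaining) divided by the number due since the dispense date; a participant is adherent if this ratio is within 20% of full intake.* Preferably report the continuous proportion as well, since it does not depend on a cut-off.

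Reconcile the wording with Procedures so that both sections describe the same adherence quantity. This is about the metric only; no view is offered on the titration rule.

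The cost is one sentence. Pill counts, dosage and dispense date are already in use. The quantity dispensed is also needed, but the present rule cannot give an expected remainder without it either. No new visit or measurement is required.
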